### Safety assessment

All subjects will be followed up by medical personnel including a chief physician throughout this study. Although LMWH is the preferred anticoagulant drug for pregnant women, we do not rule out that its use could cause some side effects. The commonly reported adverse reactions of LMWH use were blooding, and less common adverse effects include heparin-induced thrombocytopaenia, osteoporosis, and spontaneous fractures. Patients will be well informed of the potential risks in advance. Follow-up will be performed in the outpatient department at weeks 2, 4, 6, 8, and 10 after FET to record any local and/or systemic reactions during medication and any adverse events defined as below.

#### Adverse events

Adverse events(AEs) are defined as any discomfort or worsening of existing discomfort during the study period (including ovulation induction cycle, FET cycle, and follow-up), regardless of whether associated with the study intervention or not. Discomfort may be symptomatic (e.g., abdominal pain, abdominal distension, chest distress), physical signs (e.g., mobility dullness positive, adnexal mass) or abnormal examination (e.g., laboratory examination, electrocardiograph). Serious adverse events: adverse events occurring during the study period that meet one or more of the following criteria:

Severe IVF complications, including severe ovarian hyperstimulation syndrome (OHSS), complete ovarian torsion, and intraperitoneal bleeding. Severe OHSS is diagnosed when ovarian enlargement of ≥ 12 cm is observed and when there is clinical evidence of ascites and/or hydrothorax or breathing difficulties with or without hemoconcentration, severe hypoproteinemia, abnormal liver function, coagulation abnormalities, or diminished renal function.Serious complications of LMWH: Thrombocytopenia, damage of the liver, and kidney functionPregnancy-related complications: Massive bleeding during pregnancy, shock during pregnancy, etc. Adverse events will be reported in the appropriate section of the case report form. It is important that these records include the duration, extent, relationship to the study intervention and/or course of intervention, and any combination therapy.

If serious adverse events occurred, discontinuing or modifying allocated interventions for the participant would be carried out after the participant be fully informed.

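### The serious-adverse-event definition has no cause-neutral criterion, and one of its three headings depends on the study drug, so the same event can be classed differently by arm

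*Protocol article*

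**What the plan says.** The Adverse events section defines an AE broadly, as "any discomfort or worsening of existing discomfort during the study period", and counts it "regardless of whether associated with the study intervention or not". It then narrows to serious events: "Serious adverse events: adverse events occurring during the study period that meet one or more of the following criteria". The criteria are three headings:

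1. "Severe IVF complications, including severe ovarian hyperstimulation syndrome (OHSS), complete ovarian torsion, and intraperitoneal bleeding"
2. "Serious complications of LMWH: Thrombocytopenia, damage of the liver, and kidney" function
3. Pregnancy-related complications: "Massive bleeding during pregnancy, shock during pregnancy, etc"

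The same section sends AEs to the case report form, with duration, extent and relation to the intervention. It also provides that after an SAE the woman's assigned treatment would be stopped or changed once she has been informed.

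The Safety assessment section describes the expected harms of the drug: "The commonly reported adverse reactions of LMWH use were blooding, and less common adverse effects include heparin-induced thrombocytopaenia, osteoporosis, and spontaneous fractures".

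Under Randomization and allocation concealment, investigators and participants know the allocation. The control arm has hormone therapy only.

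**The concern.** Seriousness is normally judged by what happened to the patient, whatever the cause and whichever the arm. Here it is judged by the kind of event, and for one heading by the drug held responsible. This has three consequences.

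- An event with a grave outcome that belongs to none of the three headings is not serious under the printed rule.
- One heading can be applied only by attributing the event to LMWH, which controls do not receive.
- The harm that the article itself expects most often from LMWH is only partly represented.

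At stake is the between-arm SAE comparison in an open-label trial of an anticoagulant against no added drug, where that comparison is a main part of the safety conclusion.

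**Working it through.** No arithmetic from the plan applies: the article states no SAE rate and no safety sample size. The check is to put typical events through the printed rule.

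| Event | LMWH arm | Control arm |
|---|---|---|
| Death or hospital admission unrelated to IVF or pregnancy, and not a listed LMWH complication | no heading fits | no heading fits |
| Congenital anomaly in the newborn | not named; serious only if read into heading 3 | same |
| Thrombocytopenia, liver or kidney damage, not part of an IVF or pregnancy complication | heading 2, if attributed to LMWH | no heading fits; AE only |
| Intraperitoneal bleeding as an IVF complication | heading 1 | heading 1 |
| Massive bleeding in pregnancy | heading 3 | heading 3 |
| Other major bleeding, woman not pregnant | not named | not named |

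**General criterion.** The first two rows show that outcome alone never makes an event serious. Death, threat to life, hospitalisation, disability and congenital anomaly are not criteria anywhere in the article.

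**Asymmetry.** The third row is where the arms part. Suppose there is no true difference and k such events occur in each arm. On the literal reading, heading 2 yields up to k SAEs under LMWH and 0 under control. The actual LMWH count depends on attribution. If the unblinded investigators make it, it is made knowing the arm. A blinded assessor could not apply the heading at all, because it requires knowing who received LMWH. The heading also sits badly with the AE rule just above it, which disregards cause.

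**Bleeding.** The Safety assessment section gives bleeding as the common reaction, followed by thrombocytopenia, osteoporosis and fractures. Of these, only thrombocytopenia reaches heading 2. Bleeding appears under headings 1 and 3 alone, in the two forms shown. Under Interventions, LMWH starts on the progesterone transformation day and runs until a negative hCG test or ultrasound proof of intrauterine pregnancy. A woman whose hCG is negative therefore has all her exposure outside pregnancy, and a major bleed elsewhere than in the peritoneum is not named for her.

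**Direction.** The asymmetry tends to add SAEs to the LMWH arm. The bleeding gap tends to remove them from the arm where bleeding is expected. The net direction cannot be read from the document.

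**The case against.** Several stronger readings are tempting, and the text does not support them.

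- *The list is closed.* The headings are the only routes to serious, but heading 1 is introduced by *including* and heading 3 ends in *etc.* A thromboembolic event, for instance, might be placed under either. Only the set of three headings is fixed.
- *Bleeding outside pregnancy is left out.* Intraperitoneal bleeding is named with no pregnancy condition. The gap concerns other major bleeding.
- *The data safety monitoring board would miss these harms.* AEs are recorded whatever the cause, on the case report form and at visits in weeks 2, 4, 6, 8 and 10 after transfer. The board reviews safety data, not SAEs alone. A control woman's platelet fall would still be recorded; its label is what differs.
- *The arms are not comparable on safety.* Headings 1 and 3 and all AEs are arm-neutral. The asymmetry is confined to heading 2, which could also be read as a mere caption over named events.
- *Stimulation-phase events will contaminate the comparison.* The AE period does run "during the study period (including ovulation induction cycle, FET cycle, and follow-up", and randomisation comes later. But the article states no by-arm tabulation of those events, and such detail commonly sits in an analysis plan.
- *The planning rates give the size.* Women without ongoing pregnancy include those who conceived and then miscarried, so they do not count women with a negative hCG.

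It can also be said that an article condenses a fuller protocol. That would excuse silence. It does not excuse a definition that is printed and, if followed as printed, misclassifies events.

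These objections narrow the point. They do not supply a cause-neutral criterion, make heading 2 applicable to controls, or bring the two sections into line on bleeding.

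**Conclusion.** The point holds as a fault in how seriousness is classified. The printed rule lacks a general criterion, ties one heading to the study drug, and does not match the article's own account of expected LMWH harm. SAE counts can therefore be biased between arms, and some grave events can be left out of them while still being recorded as AEs. The primary outcome and its analysis are untouched.

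The size in events cannot be stated without event rates. The conclusion rests on two assumptions: that heading 2 is applied as worded, and, for the bias from unblinded attribution, that the investigators judge relatedness. The article does not name who does so, and its Discussion describes follow-up staff as blind to treatment. The asymmetry on the literal reading does not need the second assumption.

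**What to change.** Replace the three headings as the test of seriousness with outcome-based criteria applied identically in both arms: death, life-threatening event, hospitalisation or its prolongation, disability, congenital anomaly, or other medically important event. Keep the present items as examples, and remove attribution to LMWH as a condition. Relation to the intervention stays where it already is, as a separate field on the case report form. Reconcile the Safety assessment and Adverse events sections on bleeding.

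The cost is an amendment to protocol and form wording and a few more SAE reports. AEs are already recorded with duration and extent, so past events could be reviewed against the new criteria. There is one real consequence: the article links SAE status to stopping or changing the assigned treatment, so a wider definition widens that link. The sponsor must reconcile that sentence with the new definition; this review takes no position on the treatment rule.

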### Data collection and monitoring

Data Safety Monitoring Board (DSMB) is consisted of a group of independent experts external to this trial assessing the progress, safety data, to ensure problems will be addressed in an unbiased way by the trial leadership. Besides, in this trial, Clinical Trial Steering Committees undertake the primary responsibility for designing the study, maintaining the quality of study conduct, and ongoing monitoring of individual toxicities and adverse events. Protocol committee will be responsible for protocol setting and correction and also writing.

Baseline characteristics of patients will be collected, including age, BMI, parity, and education levels. Also, detailed IVF process and outcomes will be recorded in time*.* Once a patient is enrolled, a staff team will be prespecified for the follow-up and data collection. Meanwhile, the auditor will conduct data verification and quality check from time to time. The investigator and the monitor work together to ensure information of case report form (CRF) is accurate and clear. Data corrections or additions to CRF must be made by qualified researchers, signed with initial and dated. Data editing, input, and validation are performed continuously and rapidly in the study. Any missing, impossible, or inconsistent data in the CRF will be asked of the investigator via the Data Query Form and then archived for each subject until data cleansing is complete. Clinical research integration platform is used for data entry and management.

The informed consent is compliance with the relevant data protection and privacy laws. All study-related information will be stored securely at the study site. All participant information will be stored in locked file cabinets in areas with limited access. All laboratory specimens and data collection will be identified by a coded identification number to maintain participant confidentiality. All records that contain names or other personal identifiers will be stored separately from study records identified by code number. Participants’ study information will not be released outside of the study without the written permission of the participant. Participants will authorize the collection, use, and publication of the study data by the investigator and those who need the information for the study. Written informed consent will be obtained from patients before study enrollment.

During the trial, protocol amendment will be performed if the most relevant and critical modifications that affect the trial design and data collection procedure occurred. A modified version will be submitted to the Ethics Committee of The International Peace Maternity and Child Health Hospital for ethics approval and to the data monitoring committee. By video or live sessions to ensure that interested parties are known and well understood important protocol changes. The revised protocol would be printed and sent to interested parties.

### Statistical analysis

The study data are collected and managed by nonclinical staff who are responsible for data management in each clinical center. In case of missing values of baseline characteristics, we will analyze them by excluding the missing values, then assign the missing values multiple times, and conduct subsequent analyses to estimate the robustness of the results. For follow-up loss and protocol violation, we will attempt sensitivity analysis to explore the influence of these factors on the trial results.

Baseline characteristics will be described by descriptive analysis, and the balance among groups or subgroups will be assessed by analysis for different kinds of data. Continuous variables with normal distribution are presented as means with standard deviations (SDs) and continuous variables non-normally distributed as medians and interquartile ranges (IQRs). Categorical variables are presented in the form of *n* (%). The result will be analyzed according to the intention-to-treat (ITT) principle. The primary outcome (the ongoing pregnancy rate) and categorical secondary outcomes will be compared between groups by means of log-binomial regression. Adjusted risk ratios (aRRs) and unadjusted risk ratios (RRs), as well as their associated 95% confidence intervals (CIs), will be presented. And the 95% CI of the absolute rate differences (ARDs) will be used to evaluate if the LMWH group is superior to the control group. Continuous data with normal distribution will be analyzed using a two-sample *t*-test, and the Mann-Whitney *U*-test will be used for non-normally distributed data. Subgroup analysis is planned in cases categorized by year (≥ 35 years, < 35 years) and BMI (< 25, ≥ 25). To test the potential interaction between subgroups and treatment effect, we will fit a model with fixed effects to compare the treatment arms with respect to the primary outcome of the ongoing pregnancy rate and binary secondary outcomes (e.g., rates of live birth, preterm delivery, pregnancy complications, and early pregnancy loss). Statistics will be run using SPSS version 21 software (SPSS, Inc., Chicago, IL, USA). *P*-values of less than 0.05 were considered to be statistically significant.

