### Randomization and allocation concealment

PCOS women meeting the inclusion criteria will be recruited and randomized according to an online Central Randomization System stratified by the study sites and women’s age (35 years), supported by Shanghai Clinical Research Center, on the day of progesterone transformation. Participants are assigned in a 1:1 ratio randomly to the study group (LMWH + hormone therapy) or the control group (hormone therapy). LMWH is given daily subcutaneous starting from the progesterone transformation day. The dynamic block method is used to develop the randomization scheme, and the multicenter electronic random system is used to stratify the subjects within the block. Both investigators and participants are unblinded for the allocation of the intervention, while the biostatistician will be blinded to the group allocation.

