## Discussion

To our knowledge, this is the first study protocol to investigate the efficacy of LMWH as an adjuvant drug for IVF-FET outcomes in PCOS women. PCOS is one of the most important causes of female infertility. Increased risk of embryo implantation failure and early embryo loss rates were revealed by previous studies in patients with PCOS. Hypercoagulability and prethrombotic state might contribute to in PCOS patients’ pregnancy loss. LMWH preventative treatment was empirically used in RSA patients and partly showed positive results.

Our retrospective case-control study showed that significant higher clinic pregnancy rate and livebirth rate in LMWH group (supplemented with LMWH from the day of progesterone transformation) compared with those of control group. LMWH treatment seems to reduce the early pregnancy loss in IVF-FET. Therefore, it is speculated that for PCOS infertility women with prethrombotic state and associated immune dysfunction, LMWH may help to improve membrane microcirculation during peri-implantation and enhance embryos development. However, so far, there are limited data for the administration of LMWH for FET cycle in PCOS patients. Therefore, a randomized controlled trial is designed to prospectively evaluate the effect of LMWH on the IVF outcomes of FET cycles, including ongoing pregnancy rate, clinical pregnancy rate, live birth rate, and early pregnancy loss rate.

The strengths of the present study include that this is a multicenter, central dynamic randomized trial. Age, BMI, and subcenters were designed as block factors for minimizing bias. There are also some limitations: For LMWH is given subcutaneous, although good adherence in patients, it is not suitable for blind design. The nature of the LMWH treatment is open to treating physicians but blind to embryologists, laboratory technicians, and follow-ups of this study; the study population is Han of ethnic, and further studies are necessary to verify our conclusions correction in other ethnic populations, with varied genotype and phenotype.

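### Missing baseline values are excluded first and imputed only as a check, so adjusted and BMI-based analyses can lose randomised women whose outcome is known

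*Protocol article*

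**What the plan says.** All the rules on analysis stand in the Statistical analysis section of the protocol article.

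- **Missing baseline characteristics:** "we will analyze them by excluding the missing values, then assign the missing values multiple times". The purpose of the second step is to "conduct subsequent analyses to estimate the robustness of the results".
- **Analysis principle:** "The result will be analyzed according to the intention-to-treat (ITT) principle". This is not limited to any one estimate.
- **Effect measures:** the primary outcome and the categorical secondary outcomes are compared by log-binomial regression, and "Adjusted risk ratios (aRRs) and unadjusted risk ratios (RRs), as well as their associated 95% confidence intervals (CIs), will be presented". Neither ratio is called primary, and no adjustment covariates are listed.
- **Superiority:** "the 95% CI of the absolute rate differences (ARDs) will be used to evaluate if the LMWH group is superior to the control group". The difference is not said to be adjusted.
- **Subgroups:** age (cut at 35 years) and BMI (cut at 25), with models to test interaction with treatment.

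Loss to follow-up and protocol violations are dealt with separately, by sensitivity analysis.

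Three other places bear on which baseline fields could be missing. Randomization and allocation concealment says that randomisation is "stratified by the study sites and women’s age (35 years"). The Discussion says "Age, BMI, and subcenters were designed as block factors for minimizing bias", and the Abstract also names BMI as a stratifier. Data collection and monitoring lists age, BMI, parity and education as baseline data.

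**The concern.** A missing baseline covariate is not a reason to lose a randomised outcome. With exclusion first, a woman who lacks one covariate leaves every model that contains it, even if her pregnancy outcome is recorded. This has three consequences.

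1. The adjusted estimate no longer covers all randomised women with an outcome, although the section commits to intention to treat without qualification.
2. The unadjusted and adjusted risk ratios will be shown side by side but may describe different women. A difference between them could then reflect who was dropped rather than the adjustment.
3. Precision is given up in the adjusted and BMI-based analyses for no gain. Allocation is independent of baseline values, so filling in a baseline covariate without regard to arm keeps these women and does not favour either group.

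**Working it through.** **Step 1: which analyses does the rule reach?** Set the article's analyses against the baseline data that each one needs.

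| Analysis | Baseline data needed | Can exclusion drop women with a known outcome? |
|---|---|---|
| Unadjusted risk ratio | none | No |
| Absolute rate difference, if unadjusted | none | No |
| Adjusted risk ratio, site and age only | known at randomisation | No |
| Adjusted risk ratio with BMI, parity or education | may be incomplete | Yes |
| BMI subgroup and interaction models | BMI | Yes, if BMI is missing |

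Whether BMI must be known at randomisation cannot be settled. The randomisation section names only site and age, while the Abstract and the Discussion add BMI. Parity and education are stratifiers nowhere, but the article does not say that they are model terms either.

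**Step 2: reproduce the planned sample size.** The inputs from Sample size calculation are 45% against 30%, α = 0.05, β = 0.20 and 10% loss. α is taken as two-sided, which the article does not state but which reproduces its figure.

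- n per group = (1.960 + 0.842)² × (0.45×0.55 + 0.30×0.70) / 0.15² = 159.6, so 160.
- 160 / (1 − 0.10) = 177.8, so 178 per group and 356 in total, as stated.

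The 10% is described as covering loss to follow-up and dropout. Missing covariates are not mentioned.

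**Step 3: size of a loss, if there is one.** The article gives no rate of missing baseline values, so the share m is an assumption. With standard errors proportional to 1/√n, the confidence interval widens by the factor 1/√(1 − m).

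| Assumed m | Women per group (from 160) | CI width factor |
|---|---|---|
| 5% | 152 | 1/√0.95 = 1.026 |
| 10% | 144 | 1/√0.90 = 1.054 |
| 15% | 136 | 1/√0.85 = 1.085 |

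**Step 4: the same loss expressed as power.** Power = Φ(0.15/√((0.45×0.55 + 0.30×0.70)/n) − 1.96). This gives 80.1% at n = 160, 78.1% at 152, 75.8% at 144 and 73.4% at 136. A formula with pooled variance under the null gives 79.5%, 77.4%, 75.1% and 72.7% for the same shares. Both formulas describe an unadjusted comparison of two proportions, which loses nobody to a missing covariate. They also ignore any precision gained by adjustment. They show the cost of a smaller sample in general and do not give the power of the trial's superiority test.

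**The case against.** A reader might infer that the trial's primary analysis drops randomised women and so is not intention to treat. The article does not support that. It does not make the adjusted analysis primary, and its superiority criterion is the interval for the absolute rate difference, which is not said to be adjusted. It also names no covariates, and with site and age alone nobody would be dropped. This part of the objection stands in full, and it limits the point to the adjusted and BMI-based analyses.

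The sentence on missing data can also be read as omitting missing entries when baseline characteristics are summarised, since it speaks of excluding values rather than women. That reading cannot be ruled out. It is the weaker one, because the imputed analyses are there to test the robustness of results, and multiple imputation has little use in a descriptive table.

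Missing data may also be rare. Table 1 schedules demographics, history and physical examination at enrolment, and Data collection and monitoring has missing entries queried until cleaning is complete. So nothing supports a high missing rate, and the shares of 5% to 15% remain illustrations. Finally, multiple imputation is already planned, so both versions will exist. What is left is which of them is the main analysis and which is the check. That choice still matters, because the article states it and states it the less useful way round.

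**Conclusion.** The point holds as a minor one. Read as applying to the outcome models, the stated order makes complete-case analysis the main version of any model with an incomplete baseline covariate. Such a model can leave out randomised women with known outcomes, which sits badly with the intention-to-treat statement and can put the two risk ratios on different women.

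The effect is conditional on two things that the article does not settle: that some baseline values are missing, and that a model uses them. Its size is therefore unknown. If 5% to 15% of women were affected, intervals would be about 3% to 8% wider. The unadjusted risk ratio is untouched, and so is the absolute rate difference if it is unadjusted. The power figures in the working should not be read as a loss of power for the superiority decision.

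**What to change.** Reverse the order in one sentence of the Statistical analysis section or of the analysis plan. The main adjusted analyses should include every randomised woman with an outcome, with missing baseline covariates imputed, and the complete-case analysis should be the sensitivity check. Multiple imputation serves, and so does simple mean or missing-category imputation done without regard to arm. For the BMI subgroups multiple imputation is the better choice, because a single mean would place every woman with missing BMI on the same side of the cut.

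The same sentence should say whether the absolute rate difference that decides superiority is adjusted, and which covariates enter the adjusted models. Multiple imputation is already planned, so the extra analysis work is negligible. No change to data collection or sample size is needed.

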With more attention paid to the high incidence of cardiovascular diseases in PCOS patients, the disorder of coagulation system in PCOS patients has been proved in several studies. A pre-thrombotic state was proposed during PCOS women, which was manifested by increased activity of plasminogen activating inhibitor-1 (PAI-1) and fibrinogen. As a major inhibitor of fibrinolysis, the increase of PAI-1 is associated with low fibrinolysis, suggesting a high risk of thrombosis, while the increase of fibrinogen increases fibrin formation, plasma viscosity, and platelet aggregation, leading to hypercoagulability [4]. Low sex hormone-binding globulin (SHBG) and high insulin may partly explain the body mass index (BMI) independent difference of PAI-1 activity between women with PCOS and control group. It was also reported that the thrombin production rate of PCOS women was faster than that of non-PCOS ones, suggesting a higher risk of thrombosis [5]. Other researchers suggested that PCOS was an autoimmune disease [6], which was associated with a variety of autoimmune diseases, such as systemic lupus erythematosus and Hashimoto’s thyroiditis. Women with PCOS were proved to be involved in increased antibody levels, including antinuclear antibodies, antithyroid antibodies, anti-smooth muscle, anti-histone and anti-double-stranded DNA antibodies, also overactivation of the immune system, and pathophysiology of varying degrees of vascular endothelial damage. It is well known microthrombus formation in uterine embryo and placental circulation is closely related to pregnancy loss including RSA, fetal growth restriction, gestational hypertension, placental abruption, and stillbirth [7]. Therefore, changing the prethrombotic state of PCOS through anticoagulation may provide a new idea for improving pregnancy outcomes of PCOS.

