**Fig. 1 Fig1:**
[figure not shown]
Flowchart of the study

**Table 1 Tab1:** Schedule of enrollment, interventions, and assessments

Unique form	Study period							
	Enrollment	Intervention phase		Follow-up				
		Ovarian stimulation	Frozen embryo transfer	2 weeks after FET	4 weeks after FET	10 weeks after FET	28 weeks of gestation	Perinatal period
Eligibility screen	𝙓							
Informed consent	𝙓							
Demographic characteristics	𝙓							
Medical/treatment history	𝙓							
Physical exam	𝙓							
Ultrasound	𝙓		𝙓	𝙓	𝙓			
Basic sex hormone	𝙓		𝙓	𝙓	𝙓			
Coagulation function assessment	𝙓		𝙓	𝙓	𝙓			
Safety test	𝙓							
IVF treatment		𝙓						
Randomization			𝙓					
Frozen embryo transfer			𝙓					
Pregnancy evaluation				𝙓	𝙓	𝙓	𝙓	
Perinatal data collection								𝙓

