### Outcome measures

The primary outcome will be the ongoing pregnancy rate resulting from the FET cycles, which is defined by the presence of a gestational sac with a fetal heartbeat after 12 weeks of gestation. Secondary outcomes include live birth rate, preterm delivery, pregnancy complications, and early pregnancy loss rate. Live birth rate is defined as the percentage of birth cycles with at least one surviving birth to transplant cycles in the number of transplant cycles. Preterm delivery is defined as a delivery of gestational age of less than 37 weeks. Pregnancy complications mainly refer as preeclampsia (PE) and gestational diabetes (GDM). PE is defined by the combination of gestational hypertension and proteinuria occurring after 20 weeks of gestation. GDM is made when any of the following plasma glucose values are met or exceeded: (1) fasting: 92 mg/dL (5.1 mmol/L); (2) 1 h: 180 mg/dL (10.0 mmol/L); and (3) 2 h: 153 mg/dL (8.5 mmol/L). Early pregnancy loss is defined as loss of the embryo before 12 weeks of gestation, and early pregnancy loss rate refers to the percentage of early pregnancy loss cycles in the number of clinic pregnancy cycles.

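### Any between-arm comparison of coagulation or hormone values would gain precision from the enrollment value already collected; the stated tests are valid but do not use it (minor, free improvement)

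*Protocol article*

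**What the plan says.** The Statistical analysis section gives one rule for continuous variables: "Continuous data with normal distribution will be analyzed using a two-sample" t-test, with the Mann-Whitney test where the data are not normal. It mentions no covariate, baseline value or change score. For the binary outcomes the same section specifies log-binomial regression and adds: "Adjusted risk ratios (aRRs) and unadjusted risk ratios (RRs), as well as their associated 95% confidence intervals (CIs), will be presented".

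Every outcome in the Outcome measures section is binary. The primary is stated as "The primary outcome will be the ongoing pregnancy rate resulting from the FET cycles", and the secondary outcomes are live birth, preterm delivery, pregnancy complications and early pregnancy loss. The repeated laboratory assessments appear only in Table 1, in the rows "Coagulation function assessment" and "Basic sex hormone". Each row is marked at enrollment, at frozen embryo transfer, and 2 and 4 weeks after transfer.

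The Randomization and allocation concealment section places randomization "on the day of progesterone transformation", which is also when the heparin starts. The enrollment measurement therefore precedes both allocation and treatment.

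**The concern.** A two-sample test on a follow-up value ignores what is already known about each woman before allocation. When the same measure has been taken earlier, the part of the between-woman variation that the earlier value predicts can be removed from the comparison. Leaving it in makes the confidence interval wider than it need be. A Mann-Whitney test, used as a test alone, also gives no between-arm difference in the units of the measure.

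The rationale gives these comparisons some interest. The Background argues that "changing the prethrombotic state of PCOS through anticoagulation may provide a new idea for improving pregnancy outcomes of PCOS", and the coagulation row is the scheduled assessment closest to that idea. If the investigators compare the arms on it, they will want the estimate to be as precise as the collected data allow. At stake is the efficiency of a supporting laboratory comparison, not the trial's main conclusion.

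**Working it through.** **The plan's own figure.** The only sample-size figure is for the binary primary outcome: 45% against 30%, α = 0.05, power 0.80, 10% loss. With unpooled variance and a two-sided test:

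n = (0.45 × 0.55 + 0.30 × 0.70) × (1.96 + 0.84)² / 0.15², which rounds up to 160 per group; 160 / 0.90 = 178.

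This reproduces the stated 178 per group and 356 in total. The document gives no figure for any continuous comparison, so there is nothing further to reproduce.

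**Is the enrollment value a legitimate covariate?** Table 1 places it at enrollment, and randomization comes later, on the day progesterone starts. It cannot be affected by allocation. The value in the transfer column is less safe, because heparin starts on the randomization day and that sample may follow the first dose.

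**Size of the gain.** Inputs: n = 160 per arm (178 less 10%), used as an illustration for week 2; r, the correlation between enrollment and follow-up, assumed over 0.2 to 0.7; an illustrative true difference of 0.3 SD, also assumed.

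- Variance relative to the unadjusted comparison: 1 − r²
- Interval width relative to the unadjusted comparison: √(1 − r²)
- Smallest difference detectable with 80% power, in SD units: √(2/n) × (1.96 + 0.84) × √(1 − r²)
- Power: Φ(0.3 / √(2(1 − r²)/n) − 1.96)
- Equivalent n per arm for an unadjusted test: 160 / (1 − r²)

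| r | Variance saved | Relative interval width | Detectable difference (SD) | Power at 0.3 SD | Equivalent n per arm |
|---|---|---|---|---|---|
| 0 (unadjusted) | 0% | 1.00 | 0.313 | 76.5% | 160 |
| 0.2 | 4% | 0.98 | 0.307 | 78.2% | 167 |
| 0.3 | 9% | 0.95 | 0.299 | 80.3% | 176 |
| 0.5 | 25% | 0.87 | 0.271 | 87.3% | 213 |
| 0.7 | 49% | 0.71 | 0.224 | 96.4% | 314 |

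**Where in the range?** The document does not settle it. Ovarian stimulation, egg collection and embryo freezing lie between enrollment and follow-up, and the follow-up samples fall in a hormone-prepared cycle or early pregnancy. A low correlation, and so a small gain, is plausible.

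**Which visit?** The Abstract continues treatment and schedules the later ultrasound only after a positive pregnancy test, and the Interventions section ends heparin at a negative one. The Safety assessment section lists visits at weeks 2, 4, 6, 8 and 10 but does not say that blood is drawn from women who are not pregnant. Week 4 values may therefore come from a subset selected after randomization. The figure of 160 per arm cannot be carried over to that visit.

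**The case against.** The strongest objection is that the document plans no coagulation or hormone comparison. Neither measure is an outcome, the stated aims concern pregnancy and birth rates, and the sentence on continuous data does not say which data it covers. It may be meant for one-time variables, such as details of the IVF process, for which there is no earlier value to adjust for. Table 1 does not list individual assays, so that the same assay is repeated is inferred from the shared row label. An unadjusted test in a 1:1 randomized trial is valid, and covariates for an unlisted laboratory measure could be left to an analysis plan.

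Most of this stands, and it is why the point is conditional and minor. It does not remove the point, because the article does not leave the method open: it names an unadjusted test for continuous data as a class, and the two repeated rows in Table 1 are the evident post-randomization continuous data.

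A reader might infer three stronger things that the documents do not support:

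- **That the trial's check of its mechanism is undermined.** No such check is defined. The Background's markers are PAI-1, fibrinogen and thrombin production, and nothing says the coagulation panel includes them all. The row may serve clinical monitoring.
- **That the unadjusted result would be biased by chance baseline differences.** It would not. Randomization makes the test valid, and its standard error already allows for such differences.
- **That one repeated-measures model over weeks 2 and 4 with all evaluable women is the natural remedy.** The possible selection at week 4 rules that out unless blood is drawn regardless of the pregnancy result.

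**Conclusion.** The point holds as a minor, essentially free improvement. The named tests are valid but less precise than the scheduled data allow for any between-arm comparison of post-randomization coagulation or hormone values. The variance saving is r squared: from 4% at r = 0.2 to 49% at r = 0.7. Its size cannot be fixed from the document, since r is not given. The 0.3 SD difference and the 160 women per arm at week 2 are also illustrative assumptions.

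The direction is safer than the size: in large samples with 1:1 allocation, ANCOVA does not lose precision. The conclusion also assumes that each Table 1 row refers to the same measure at each visit.

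**What to change.** Add to the Statistical analysis section: where post-randomization coagulation or hormone values are compared between arms, the comparison will use ANCOVA with arm, the enrollment value of the same measure, site and age stratum, and will report the adjusted difference with its 95% confidence interval. If a measure is skewed, analyze it on a log or rank scale. The choice between these is a preference, though a log scale gives a ratio that is easier to interpret. Keep the t-test or Mann-Whitney test for continuous data without a baseline.

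Apply the model mainly at week 2. State whether week 4 samples are drawn from all women, and treat week 4 values as descriptive if they come only from those with a positive pregnancy test. Use the transfer-visit value as baseline only if it was drawn before the first heparin dose.

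The cost is a few sentences, settled before data by arm are examined. No new visits, samples or software are needed. The section already plans multiple imputation for missing baseline characteristics, which can be extended to a missing enrollment value. The model adds five parameters (three for the four sites, one for age stratum, one for the enrollment value), which is little against 2 × 160 = 320 women.
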